## Discussion

### Principal Findings

The anticipated outcomes of this study are the identification of associations and the development of combination models between quantitative ultrasound and blood-based assays with multifactorial clinical assessments, specifically focusing on muscle quality and frailty. The use of noninvasive portable technologies facilitates the implementation of the clinical protocol in both hospital and primary care environments [92].

The primary findings concerning the correlations of ultrasound geometric variables with clinical and functional variables align with existing clinical literature [17,35,36,41]. These preliminary results are encouraging, demonstrating robust correlations between echo geometric parameters, measured in a standardized manner, and various clinical parameters. Notably, moderate correlations are observed between ultrasound geometrical parameters and muscle mass (DXA), while functional parameters and global scales of sarcopenia and frailty exhibit weak yet significant associations. These results serve as a foundational baseline for the development of advanced models based on raw data (Table 1) and blood biomarkers. It is anticipated that these advanced models will exhibit superior correlations with basal characteristics and enhanced sensitivity to changes in muscle quality.

### Comparison With Prior Work

Recent literature indicates that impaired mobility associated with aging is not solely attributed to changes in skeletal muscle mass; other factors contributing to muscle quality also play a crucial role. Notably, alterations in muscle tissue composition, characterized by elevated levels of intramuscular adipose tissue and intramyocellular lipids, have been identified as factors that negatively impact muscle functional capacity [17,65,93]. Our hypothesis suggests that quantitative ultrasound biomarkers derived from raw data may exhibit superior discriminative performance, greater reproducibility, and enhanced ease of use compared with the current state-of-the-art assessments based on B-mode images. B-mode morphological ultrasound parameters are primarily linked to muscle mass and demonstrate limited sensitivity in the diagnosis of sarcopenia. Quantitative ultrasound biomarkers derived from raw data have consistently demonstrated their ability to capture both tissue composition and microstructural properties. Furthermore, they have exhibited a greater capacity to encode richer information content compared with ultrasound B-mode images in artificial intelligence models, as highlighted in prior research [52,54,83,84]. Ultrasound spectroscopy parameters and tissue acoustic properties, such as speed of sound and attenuation, have been associated with tissue composition [47] and viscoelastic changes in muscle [49] among older individuals with sarcopenia. Specifically, speed of sound has demonstrated correlations with MRI adiposity estimates in the calf muscles [94], CT assessment of the psoas muscle [95], and short-term changes in muscle due to immobilization [96]. The ultrasound statistical analysis of the envelope signal in soft tissues has been correlated with the concentration, spacing, and directionality of microstructural scatterers [78]. Additionally, texture features derived from radiomics analysis capture musculoskeletal composition and microstructure. This approach has been successfully applied to differentiate various musculoskeletal conditions, including muscle spasticity, dynapenia, myositis, fibromyalgia, Duchenne muscular dystrophy, and exercise-induced muscle damage [55,97]. Being acquired at the early stages of ultrasound image formation, ultrasound raw data may play a crucial role in minimizing equipment- and operator-dependent bias. Additionally, they have the potential to provide data-based guidance for examiners with limited sonographic acquisition expertise.

Molecular biomarkers obtained from blood assays are linked to functional changes between healthy individuals and those with frailty. However, the absence of single established predictor biomarkers is primarily attributed to several factors. These include the heterogeneity and limitations of the scales or indices used to detect sarcopenia and frailty; variations in age, sex, and characteristics across different populations; small sample sizes; limited longitudinal clinical studies; a lack of characterization on interventions to assess their potential reversibility; and differences in techniques and cut-offs used for biomarker measurement. In this study, we incorporate a panel of biomarkers rather than assessing individual molecules. This approach is aimed at providing a more comprehensive reflection of the accumulation of damage associated with age-related syndromes [98]. Additionally, the potential of these biomarkers to assess reversibility, a critical characteristic of frailty, will be evaluated upon completion of an intervention based on an exercise program, followed by a 16-week follow-up.

Sarcopenia and frailty, although related, are distinct aging phenotypes. Notably, the prevalence of sarcopenia is higher among older individuals with frailty than the prevalence of frailty among those with sarcopenia [28-32]. As part of our exploratory outcomes, we will consider the coexistence of sarcopenia and frailty, redefining the frailty prognosis based on the presence or absence of sarcopenia.

To the best of our knowledge, this cohort study stands out as one of the few that integrates raw data ultrasound measurements with blood samples to extract noninvasive biomarkers of frailty and sarcopenia in older adults. Notably, this study represents the first of its kind to establish a connection between quantitative ultrasound and blood biomarkers with the cross-sectional evaluation of frailty and sarcopenia in both hospital and primary care environments. The utilization of point-of-care ultrasound devices presents an opportunity to introduce ultrasound quantitative technology across various clinical settings. Notably, this study marks the pioneering effort to combine quantitative ultrasound with blood-based biomarkers to evaluate musculoskeletal changes following multicomponent physical exercise programs.

### Limitations

The study does have certain limitations, notably the absence of access to a gold standard for muscle quality assessment. Established radiological techniques such as CT and MRI serve as references for muscle composition and microstructure but come with patient complications and are not widely accessible in the clinical environments under investigation. Instead, we rely on a multifactorial clinical assessment, patient stratification, and carefully controlled interventions to evaluate changes in muscle quality. The exploration of ultrasound technology is limited to backscattering ultrasound data derived from beamformed raw data. Other ultrasound quantitative technologies, such as shear wave elastography [43] and blood flow measurements based on Doppler sequences [99], are excluded from the scope because of their lack of routine availability in point-of-care ultrasound devices and the added complexity they introduce to the protocol execution. The disparate monitoring periods in hospital (16 weeks) and primary care environments (1 year) are designed to accommodate the distinct follow-up workflows in both settings. We also acknowledge that the randomization of populations in the secondary goal is conducted on an institutional basis, which could introduce statistical bias if the populations in the 2 institutions differ. To address this potential bias, we will perform a *post hoc* analysis to examine the characteristics of the populations in the various recruitment centers. The dimensioning of the primary care follow-up aligns with periods established in previous studies for the general population [89,90].

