#### Hospital Control Cohort

Participants will be consecutively recruited from the scheduled patient list of the frailty unit, day hospital, and the outpatient clinic of the Geriatrics Department of hospital 2. Upon obtaining informed consent, baseline study variables will be collected. These patients will be followed up for 16 weeks under usual care. After the follow-up period, a repetition of the baseline evaluation will be conducted.

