**1. Inclusion criteria**
Age of at least 70 years.Either gender.Ability to provide informed consent.Ability to perform all the functional tests.In the hospital exercise cohort, the ability to participate in the physical exercise program.

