**2. Exclusion criteria**
Expected survival of <1 year.Barthel Scale score <70.Moderate-to-severe cognitive impairment.Refusal to participate.Medical conditions that may compromise or impede follow-up assessments.Older adults already enrolled in regular physical exercise programs will be excluded from participating in the hospital exercise cohort.

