### Allocation

The allocation sequence in this multicentric study is institution-based. Patients recruited at the Department of Geriatrics of the Complejo Hospitalario Universitario de Albacete will be automatically allocated to the supervised exercise program by default. By contrast, patients recruited at the Geriatrics Department of the University Hospital of Getafe will not be assigned to any specific interventions. Similar sociodemographic characteristics are anticipated for both patient populations. At each institution, patients will be recruited from the falls unit, outpatient clinics, and day hospital. Within each acquisition site, patient selection will be conducted based on the clinical agenda until the recruitment goals are met.

The allocation sequence is sequential, aligned with the clinical agenda, and overseen by the clinical principal investigator at each site. Any deviations from the recruitment plan outlined in the clinical agenda must be thoroughly justified and meticulously documented.

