### Statistical Analysis

The study population will be characterized based on demographic and clinical attributes. Categorical data will be summarized with frequency and percentage representations. Continuous data will be described using mean, SD, median, and the 25th and 75th percentiles. Furthermore, the distribution of ultrasound parameters with respect to the primary endpoint will be depicted using graphical techniques. The correlation of quantitative biomarkers will be evaluated for each multifactorial clinical evaluation parameter using the Pearson correlation coefficient for continuous variables and the Spearman correlation coefficient for categorical variables [88]. Unpaired tests, such as the Student *t* test, will be used for comparing means of biomarkers among various acquired patient cohorts and for stratified patient subgroups based on the frailty scales outlined in Textbox 1. To manage the extensive array of ultrasound and blood biomarkers, a robust statistical analysis plan will be implemented. This plan will incorporate correction methods to address the risk of type I errors associated with multiple comparisons. Specifically, for the primary outcome concerning biomarker-clinical associations, we will use Lasso regression. This technique automates the selection of relevant variables, reducing the necessity for extensive corrections and improving interpretability. Paired statistics will be applied in the statistical analysis for longitudinal monitoring, encompassing both interventions and clinical follow-up. The monitoring period in hospital and primary care environments will differ to accommodate the distinct follow-up workflows in each setting. The duration of primary care follow-up aligns with established norms [89,90]. To account for differences in follow-up duration among cohorts over time, our data analysis will incorporate appropriate statistical methods, potentially enabling adjustments for these variations. For the secondary objective, the impact of physical intervention in 50 patients will be compared with 50 patients with no intervention. With 80% power, the planned population size will enable the detection of a biomarker with a medium effect size of E/S=0.284 at a 2-sided α level of .05.

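### The exercise-versus-usual-care contrast is non-randomised with one hospital per arm and unequal eligibility, yet Limitations calls it randomization and meets the bias only with a post hoc description of centres

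*Protocol article*

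**What the plan says.** **Assignment.** The Allocation section states that "The allocation sequence in this multicentric study is institution-based". Patients at hospital 1 "will be automatically allocated to the supervised exercise program by default", and patients at hospital 2 receive no specific intervention. The same section expects similar sociodemographic characteristics in the two populations and gives no support for this. The Limitations section then says "We also acknowledge that the randomization of populations in the secondary goal is conducted on an institutional basis", grants that bias could arise if the two institutions' populations differ, and offers a post hoc look at the centres' characteristics to address it.

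**Eligibility.** Textbox 1 sets two criteria for one arm only. The inclusion criterion is "In the hospital exercise cohort, the ability to participate in the physical exercise program". The exclusion criterion is "Older adults already enrolled in regular physical exercise programs will be excluded from participating in the hospital exercise cohort".

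**Source clinics.** The Allocation section says "At each institution, patients will be recruited from the falls unit, outpatient clinics, and day hospital". The Hospital Exercise Cohort section names the falls unit and outpatient clinics only. Under Hospital Control Cohort, patients are "consecutively recruited from the scheduled patient list of the frailty unit, day hospital, and the outpatient clinic".

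**Analysis.** Secondary Outcomes plans a direct comparison of the two hospital cohorts. Under Statistical Analysis, "the impact of physical intervention in 50 patients will be compared with 50 patients with no intervention". That section also names unpaired tests for comparing biomarker means among cohorts and paired statistics for longitudinal monitoring. It closes with a general sentence on subgroup analyses and on regression models for covariates.

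**The concern.** This is the only contrast that can support the Abstract's aim of testing whether the biomarkers detect change after supervised exercise relative to usual care. Exercise and hospital coincide completely: hospital 1 contributes no unexercised patients and hospital 2 no exercised ones. Any difference between the hospitals in case mix, referral, usual care, measurement or natural course therefore enters the estimate.

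The wording makes this worse in two ways. *Randomization* tells the reader that chance assigned the patients. The conditional phrasing about bias suggests the populations may turn out alike, although the eligibility rules already separate them. A control already in a regular exercise programme bears directly on the comparison, because that control's course is not that of an unexercised patient. Describing the centres afterwards would show some of the imbalance and correct none of it.

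**Working it through.** **1. Passages side by side.**

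| Feature | Exercise cohort | Control cohort | What the protocol says of the pair |
|---|---|---|---|
| Assignment | all of hospital 1 | all of hospital 2 | institution-based (Allocation); randomization (Limitations) |
| Able to take part in the programme | required | not required | bias only if populations differ (Limitations) |
| Already in regular exercise programmes | excluded | not excluded | as above |
| Source clinics | falls unit, outpatients | frailty unit, day hospital, outpatients | falls unit, outpatients and day hospital at each institution (Allocation) |

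The label and the source clinics are contradictions within the document. The two eligibility rows make the populations differ by rule.

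**2. The plan's own figure for this contrast.** The protocol gives E/S = 0.284 for 50 versus 50 at 80% power and two-sided α of .05. The two-sample formula gives (1.960 + 0.842) × √(1/50 + 1/50) = 0.560, or 0.566 with the t distribution. The stated value is close to a one-sample or paired test on 100: 2.802/√100 = 0.280, or 0.283 with t. This mismatch is a separate matter. For that reason 0.284 is not used below as a yardstick for bias.

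**3. A pure hospital difference in change.** Let b be a difference in mean 16-week change, in SDs of change, that is due to hospital alone. With 50 per arm the standard error is √(2/50) = 0.2, so the test statistic is centred at 5b. The rejection rate is Φ(5b − 1.96) + Φ(−5b − 1.96). The values of b are assumptions.

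| b | 0.1 | 0.2 | 0.3 | 0.5 |
|---|---|---|---|---|
| declared significant with no exercise effect | 8% | 17% | 32% | 71% |

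With one hospital per arm, the data cannot estimate b apart from the exercise effect.

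**4. Baseline differences and regression to the mean.** Let δ be the baseline difference in outcome SDs and ρ the baseline-to-follow-up correlation. Assume equal SDs at both visits and no exercise effect.

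- If both hospitals regress to a common mean, the follow-up difference is ρδ. The change-score difference is then (1 − ρ)δ in size, and the baseline-adjusted difference is ρδ − ρδ = 0.
- If each hospital regresses to its own mean, the follow-up difference stays δ. The change-score difference is then 0, and the baseline-adjusted difference is δ − ρδ = (1 − ρ)δ.

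The size (1 − ρ)δ over assumed values, in outcome SDs:

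| δ | ρ = 0.5 | ρ = 0.7 | ρ = 0.9 |
|---|---|---|---|
| 0.2 | 0.10 | 0.06 | 0.02 |
| 0.4 | 0.20 | 0.12 | 0.04 |
| 0.6 | 0.30 | 0.18 | 0.06 |

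The same error falls on whichever analysis has the wrong assumption. The design gives no way to tell which assumption holds, so neither analysis can stand as the sole remedy.

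**The case against.** The strongest reply is that nothing is hidden. The Abstract calls the study observational, Study Setting calls it exploratory, Allocation says plainly that assignment is by institution, and Limitations itself raises the bias. This stands against any charge of concealment. It does not repair the label, or a remedy that only describes.

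A reader might infer that no adjustment is planned. The documents do not support that. Statistical Analysis does foresee regression models for covariates, no passage fixes the test for the difference in change, and a covariate list may properly sit in an analysis plan that is not shown. What remains is that this sentence is generic and not linked to this contrast, while the one response that is linked to the bias is the post hoc description.

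A reader might also infer that controls include people too limited to exercise. Textbox 1 narrows this for all cohorts: everyone must be able to perform all the functional tests, and a Barthel score below 70, moderate-to-severe cognitive impairment and conditions impeding follow-up are excluded. The firmer half of the eligibility point is that controls may already be in exercise programmes.

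Finally, a reader might expect the result to be published as a randomised effect. No passage says so.

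**Conclusion.** The concern holds in this form: a non-randomised contrast with one centre per arm is mislabelled, its populations differ by the protocol's own criteria, its recruitment sources are stated inconsistently, and the remedy tied to the bias removes none.

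The documents do not determine the size of the bias. Over assumed baseline differences of 0.2 to 0.6 SD and correlations of 0.5 to 0.9, the error from choosing the wrong one of the two standard analyses runs from 0.02 to 0.30 SD. A reader might infer that baseline adjustment would remove the bias. That holds only if both hospitals regress to a common mean, and in any case no adjustment removes a hospital effect that is not carried by measured covariates.

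This should be fixed, but it is not critical to the study, because the contrast is a secondary objective and the primary cross-sectional associations do not depend on it.

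**What to change.** 1. **Label and conclusion.** In Limitations, replace *randomization* with *non-randomised, one centre per arm*. State that exercise and hospital effects cannot be separated and that the contrast is associational. Cost: wording only.
2. **Analysis.** In place of the post hoc description as remedy, tie the covariate regression already foreseen to this contrast. Model each 16-week outcome on cohort, its baseline value and covariates already collected: age, sex, BMI, Charlson index, SPPB and frailty phenotype. Report a covariate-adjusted change-score analysis alongside. That second model must omit the outcome's own baseline value, otherwise it returns the same cohort coefficient. State that the two rest on different assumptions about regression to the mean, and treat disagreement between them as uncertainty. Cost: one extra model per outcome and no new data.
3. **Eligibility.** Record for each control whether they are already in a regular exercise programme and whether they meet the exercise-cohort participation criterion. Run a sensitivity analysis restricted to controls who meet both exercise-cohort criteria. The physical activity questionnaire is only a proxy, since it measures activity level and not programme enrolment. Recruitment began in March 2022 and was under way at submission, so flagging controls is preferable to changing eligibility midway. Cost: one or two added items, and lower precision in the restricted analysis; the documents give no figure for how many controls would be lost.
4. **Sources.** Reconcile the Hospital Exercise Cohort and Hospital Control Cohort sections with Allocation on the clinics actually used. Cost: wording only.

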### Conclusions

In summary, the outlined study protocol aims to integrate portable technologies, leveraging quantitative muscle ultrasound and blood-based biomarkers, for an objective cross-sectional assessment of muscle quality in both hospital and primary care environments. The study endeavors to yield data that will facilitate the exploration of associations between biomarker combinations and the cross-sectional clinical evaluation of frailty and sarcopenia, alongside an examination of musculoskeletal changes following multicomponent physical exercise programs.

## Appendix

Multimedia Appendix 1 SPIRIT (Standard Protocol Items of the Recommendations for Interventional Trials) checklist.

## Abbreviations

CT: computed tomography
DOCS: Definition and Outcomes Consortium
DXA: dual-energy X-ray absorptiometry
EDTA: ethylenediaminetetraacetic acid
EWGSOP-2: European Working Group on Sarcopenia in Older People 2
FRAIL: short 5-question assessment of Fatigue, Resistance, Aerobic capacity, Illnesses, and Loss of weight
GAPDH: glyceraldehyde-3-phosphate dehydrogenase
HIPAA: Health Insurance Portability and Accountability Act
MRI: magnetic resonance imaging
NIHF: National Institute of Health Foundation
PCR: polymerase chain reaction
SARC-F: Strength, Assistance with walking, Rising from a chair, Climbing stairs, and Falls
SPIRIT: Standard Protocol Items of the Recommendations for Interventional Trials
SPPB: Short Physical Performance Battery
sRAGE: soluble receptor for advanced glycation end products (sRAGE)
